## Trial size estimates for the primary hypotheses

### Hypothesis A

The outcome in this hypothesis is severe illness in the first 14 weeks of life. Based on an estimated 10% risk of severe illness in the first 14 weeks of life [65], 90% power and a risk ratio of 0.7, the required sample size is 1914 (Table 1).

**Table 1 Tab1:** Assumptions used for sample size calculation for the first 14 weeks of life

Assumption	Estimated level
Two-sided significance level	0.05
Ratio of sample size early/late BCG vaccination	1
Percent of vaccinated at 14 weeks of age with severe illness	15
Percent of vaccinated at birth with severe illness	10
Risk ratio:	0.7
Risk difference	5
Total sample size (i.e., in both trial arms)	1914

*BCG* Bacillus Calmette-Guérin

Taking into account 10% attrition and that up to 5% of the infants may have contracted HIV-1 infection when enrolled, a total of 2200 babies are required for this trial, 1100 children in each study arm.

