## Methods/design

### Hypotheses

Compared to deferring BCG vaccination until 14 weeks of age, BCG administered within the first 24 h of birth leads to at least a 30% relative risk reduction of severe illness^1^ among HIV-1-exposed infantsDelayed BCG results in at least a 30% higher production of TNF, IL-1β, IL-6, IL-10, IL-17, IL-22 and IFN-γ in response to mycobacterial (from *Mycobacterium tuberculosis* and PPD) and non-mycobacterial (from *Escherichia coli, Candida albicans* and *Staphylococcus aureus*) antigens compared to when BCG is administered at birth in HIV-1-exposed infants

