Also, autoregressive correlation approaches will be used to account for multiple and possibly correlated observations within the same study participant. These methods take the correlation structures into account and thereby the fact that measurements taken closer in time for an individual are likely to be more correlated than two measurements taken farther apart for that same individual. Efficacy will be calculated as 100 × (1 − RR), 100 × (1 − IRR) or 100 × (1 − HR). The prevalence of BCG scarring will be compared between the two study arms using the abovementioned approaches, as appropriate. Linear regression and or *t* tests will be used to compare the TNF and IFN-γ responses between the trial arms. We will consider adjusting for potential confounders if: (1) there are baseline imbalances between trial arms, (2) the variables for which there are such baseline differences are strongly associated with the study event or (3) they cause a ≥5% difference in the effect measures when they are added to the main model. Full case analyses will be default, but appropriate imputations will be considered for missing data.

In addition to the *intention-to-treat analysis*, where outcomes will be compared according to the random allocation, *instrumental variable analyses* will be conducted in an attempt to estimate biological/causal effects of the actual receipt of the vaccine. In these analyses, random allocation will be the instrument. To enable such analyses, actual receipt as well as the age of BCG vaccination will be captured in all participants. We will also perform *per-protocol* and *as-treated* analyses.

The primary analyses will include all HIV-1-exposed infants, adjusting for any imbalance in HIV-1 status between the two trial arms, as appropriate. However, we will also perform an analysis of the large subgroup of babies who remain uninfected with HIV-1.

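### The 1914 total has 90% power for a risk ratio of 0.667 (15% vs 10%); at the stated and hypothesised ratio of 0.70 its power is about 80–84%.

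*Protocol article*

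**What the plan says.** In the Protocol article, the sizing paragraph under Hypothesis A starts from an estimated 10% risk of severe illness and concludes: "90% power and a risk ratio of 0.7, the required sample size is 1914". The sentence cites Table 1 for its assumptions.

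Table 1 gives:
- "Two-sided significance level 0.05"
- "Ratio of sample size early/late BCG vaccination 1"
- "Percent of vaccinated at 14 weeks of age with severe illness 15"
- 10% for infants vaccinated at birth
- a risk ratio of 0.7 and a risk difference of 5
- a total of 1914

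The Hypotheses section says that vaccination at birth "leads to at least a 30% relative risk reduction of severe illness", which puts the boundary of the hypothesis at a risk ratio of 0.70.

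The total is then raised to 2200, 1100 per arm, to allow for attrition and HIV-1 infection.

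**The concern.** The entries in Table 1 do not all describe the same effect. Rates of 15% and 10% and a difference of 5 points belong to a ratio of 0.667. A ratio of 0.70 would give a difference of 4.5 points from 15%, or about 4.3 points with 10% in the birth arm. The smaller effect needs a larger trial, so one total cannot carry 90% power for both.

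This matters because the 90% is attached to the ratio of 0.7, in the sentence that sizes the clinical co-primary outcome, and the hypothesis has the same 30% boundary. If power at that boundary is really 80–84%, the type II error there is 16–20% and not 10%. Someone reading a null result against the stated design could then treat it as firmer evidence against a 30% reduction than it is.

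**Working it through.** **Inputs.** Two-sided alpha 0.05, 1:1 allocation, 90% power, p₁ = 0.15 (delayed), p₂ = 0.10 (birth), all from Hypothesis A and Table 1. Normal quantiles: 1.960 for alpha and 1.2816 for 90% power.

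**Formulas.** With d = p₁ − p₂ and p̄ the mean of the two risks, the uncorrected number per arm is

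n = [1.960·√(2p̄(1−p̄)) + z_β·√(p₁(1−p₁)+p₂(1−p₂))]² / d²

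and the continuity-corrected number per arm is

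n_c = (n/4)·[1 + √(1 + 4/(n·d))]².

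**Step 1: reproduce 1914.** For 15% vs 10%, p̄ = 0.125 and d = 0.05.
- n = (1.960 × 0.4677 + 1.2816 × 0.4664)² / 0.0025 = (0.9167 + 0.5977)² / 0.0025 = 917.3. This rounds up to 918 per arm, 1836 in total.
- n_c = (917.3/4)·[1 + √(1 + 4/(917.3 × 0.05))]² = 956.9. This rounds up to 957 per arm, **1914** in total.

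The match is exact. The design behind 1914 is 15% vs 10% with the continuity correction, and 0.10/0.15 = 0.667.

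**Step 2: size needed at a ratio of 0.70.** There are two ways to stay on Table 1: hold the delayed-arm risk at 15% (birth arm 0.7 × 15% = 10.5%), or hold the birth-arm risk at 10% (delayed arm 10%/0.7 = 14.29%). Total for 90% power:

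| Rates | Uncorrected | Corrected |
|---|---|---|
| 15% vs 10.5% | 2306 | 2394 |
| 14.29% vs 10% | 2438 | 2530 |

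**Step 3: power at a ratio of 0.70.** Solving the first formula for power gives

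z = [d·√n − 1.960·√(2p̄(1−p̄))] / √(p₁(1−p₁)+p₂(1−p₂)).

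For corrected power, n is replaced by (n − 1/d)²/n, which inverts the correction. With 957 per arm:
- 15% vs 10.5%: z = (0.045 × 30.935 − 0.9245)/0.4706 = 0.994, power 84.0%. Corrected: n becomes (957 − 22.2)²/957 = 913.1, z = 0.925, power 82.2%.
- 14.29% vs 10%: z = (0.04286 × 30.935 − 0.9053)/0.4609 = 0.912, power 81.9%. Corrected: n becomes 910.9, z = 0.842, power 80.0%.

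The same calculation for other numbers analysed (uncorrected / corrected):

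| Analysed | 15% vs 10% | 15% vs 10.5% | 14.29% vs 10% |
|---|---|---|---|
| 1914 | 91.2% / 90.0% | 84.0% / 82.2% | 81.9% / 80.0% |
| 1980 (2200 × 0.9) | 92.0% / 91.0% | 85.2% / 83.6% | 83.2% / 81.4% |
| 2200 (no loss) | 94.4% / 93.6% | 88.6% / 87.3% | 86.9% / 85.4% |

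Power at 0.70 stays below 90% in every row, even if no infant is lost.

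**Step 4: another route to 1914.** A ratio of exactly 0.70 (14.29% vs 10%) at **80%** power with the correction gives 956.7, so again 957 per arm and 1914. That route contradicts the stated 90% and the 15% and 5-point entries. It also puts power at 0.70 at 80%. Neither route gives 1914 with 90% power at 0.70.

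**The case against.** The strongest defence is that nothing is hidden. Table 1 prints 15%, 10%, a difference of 5 and a total of 1914, and these agree with each other. The 90% is true for those rates, and 0.7 is plausibly 0.667 rounded to one decimal. Hypothesis A says at least 30%, which a 33% reduction satisfies. The Plan of analysis commits to 95% confidence intervals, and Primary analysis adds relative and absolute effects, which limits how far a null result can be misread. The planned analyses name no continuity-corrected test, so uncorrected power (82–84% with 1914, 83–85% with 1980) is arguably the fairer figure.

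Most of this stands. It shows that the sample size is not miscalculated and that the fault is confined to a rounded ratio. It does not rescue the sentence as written, which attaches 90% to 0.7, or the hypothesis, whose boundary is 0.70.

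Three stronger readings are tempting, and the document does not support them:
- **Power near 62–65%.** A reader might take the 10% in the text as the comparator risk, giving 10% vs 7%. Table 1, cited in the same sentence, assigns 10% to the birth arm, which excludes this.
- **1914 fits no version of a 0.7 ratio.** Step 4 shows one that does, at 80% power. The supportable statement is that none does so at 90%.
- **The inflation to 2200 is contradictory or too small.** The text reads "Taking into account 10% attrition and that up to 5% of the infants may have contracted HIV-1 infection when enrolled", yet "The primary analyses will include all HIV-1-exposed infants". Taking off both losses leaves 2200 × 0.85 = 1870 or 2200 × 0.9 × 0.95 = 1881, below 1914. But an HIV-1 allowance is merely conservative for the primary set and fits the planned analysis of uninfected infants. Power for 15% vs 10% at those numbers is still 89–91%.

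**Conclusion.** The power statement is wrong as written and should be corrected. The 1914 total delivers 90% power for a ratio of 0.667, a 33% reduction. At a ratio of 0.70, power is about 80–84% with 1914 analysed (82–84% without the continuity correction) and about 81–85% with 1980 analysed. Reaching 90% at 0.70 would take about 2306–2530 infants analysed.

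These figures assume the Table 1 rates with one arm's risk held fixed, two-sided 0.05, equal arms and a simple comparison of two proportions. The spread within each range reflects which arm is held fixed and whether the correction is applied. The 1980 assumes 10% attrition and no other exclusion.

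A reader might infer that the trial is badly undersized. The document does not support that: the total is right for the rates it tabulates, and the shortfall concerns one boundary value. The point is one of accurate reporting of the design effect and does not challenge the design.

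**What to change.** Keep 2200 and make the sizing paragraph, Table 1 and Hypothesis A agree, in one of two ways:

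1. State the design ratio as 0.67 (15% vs 10%, a 33% reduction) at 90% power, and align Hypothesis A with it.
2. Keep 0.70 in Hypothesis A and the sizing paragraph, and give power as about 80–85%, naming the pair of rates used (15% vs 10.5%, or 14.3% vs 10%) and the number analysed. Correct the Table 1 rates and difference to match.

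Either way, say that the continuity correction was used, since 1914 cannot be reproduced for 15% vs 10% without it (1836).

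The cost is rewording one paragraph and one table, plus the hypothesis under the first option. Under the second, the stated power is less favourable. No infants are added, and randomization, follow-up and analysis do not change. Recruitment was already under way when the article appeared, so the change should be recorded as a clarification of the sizing assumptions.

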### Hypothesis B

The outcome for this hypothesis is the production of relevant cytokines in response to mycobacterial and non-mycobacterial antigens. Based on previous studies [33, 66] we expect that comparisons involving 50 children in each arm will be sufficient to detect biologically relevant differences.

## Randomization

Infants of HIV-1-infected mothers are randomized within 24 h of birth using pre-prepared randomization lists. Randomization is stratified by clinic using permuted blocks of varying size (4, 6 or 8). Eligible infants are allocated in a 1:1 ratio to one of the two following arms: BCG vaccination within 24 h of birth or BCG vaccination at week 14. All computer-generated randomization lists were prepared for each clinic by an independent scientist, and are kept safely off site. Concealment until the mother-infant pair has been deemed eligible for final inclusion is ensured using an application running on a dedicated Android cell phone at each clinic.

## Blinding/masking

Although scientifically advantageous, giving a placebo injection in the delayed BCG arm may be practically and ethically questionable, and the study is an open-label trial. Rigorously trained [67] research assistants who record outcomes are blinded as much as possible to which trial arm the children belong. Further, the vaccine is administered by routine health workers at the health centers that regularly administer the BCG vaccine as well as other childhood vaccines.

## Implementation plan, staff recruitment and training

### Field organization

Recruitment at each of the three health facilities is done by three full-time research assistants (nurses) and a part-time research assistant. The coordinator (ON) is responsible for the day-to-day running of the study, and will report to the principle investigator (PI; VN) and co-PI (HS) who will ensure the overall scientific integrity of the study. The study will also employ a data manager that will oversee data quality. All study staff have received intensive training on study procedures and refresher training will be conducted during the trial.

#### Screening of pregnant women

All HIV-1-positive pregnant women between 28 and 40 weeks of gestation attending antenatal care at the three clinics are informed about the study. Specifically, they are informed that if they choose to participate in the study, their infants will be randomized to receive the BCG vaccine within 24 h of birth or at 14 weeks of age. Consenting women are offered a CD4 cell count, a full blood count including hemoglobin estimation and a clinical assessment for HIV-1 disease staging and investigations for opportunistic infections, including TB. Pregnant women who are eligible following the screening and who consent to participate are recruited into the study at this first meeting. During recruitment, data on baseline characteristics and other social-demographic variables is collected.

#### Postnatal screening

Infants are assessed for other inclusion and exclusion criteria, and if eligible, randomized into the study within 24 h of birth. At birth, blood is drawn to perform a deoxyribonucleic acid polymerase chain reaction (DNA-PCR) assay for diagnosing any HIV-1 infection within 6 weeks of birth. The DNA-PCR assays are performed in batches (on samples collected over a 1-month period; Fig. 2) using standard procedures. In addition, cord blood is collected for the child’s full blood count at baseline. A sample of this cord blood is stored for future investigations.

**Fig. 2 Fig2:**
[figure not shown]
Time schedule for study procedures

## Collection of data on baseline features and potential confounders

Data on relevant baseline characteristics is collected during pregnancy and at birth. This will include indicators of socio-demographic characteristics (maternal education and age, food insecurity, income, employment, etc.), health (illness history, parity, disclosure of HIV status to a partner, clinical examination, hemoglobin, Body Mass Index (BMI), viral load, CD4 cell count), premature rupture of membranes, postpartum complications, adherence to ART and cotrimoxazole prophylaxis, sex of the child, infant feeding practices, and whether the mother received tetanus toxoid during pregnancy as per national recommendations.

## Follow-up and subject retention

Follow-up visits at the study clinic are scheduled on day 7 and at weeks 2, 6, 10, 14, 15, 26, 28, 48 and 52 after birth (Figs. 2 and 3). At each of these visits, data is collected on the primary and secondary study outcomes, adverse events (localized abscess formation, suppurative lymphadenitis and disseminated BCG infection), anthropometry and on potential confounding variables (see above). Mothers are given a cell phone to facilitate contact with study staff in case of an illness or other important child events.

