## Intervention and co-interventions

The study intervention is an intradermal administration to HIV-1-exposed babies of 0.05 ml Tubervac® BCG vaccine from the Serum Institute of India, the vaccine currently provided by the Ugandan vaccination programme. After randomization within 24 h of birth, infants in one trial arm will receive the vaccine immediately (BCG at birth) while infants in the other arm will receive the vaccine at 14 weeks of age (delayed BCG). Our study nurses, already experts in administering all childhood vaccines, including Tubervac®, will ensure that the vaccine is administered as scheduled.

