## AE monitoring, recording and reporting

Potential AEs will be carefully monitored throughout the trial with specific questionnaires. The mothers will be invited and encouraged to consult the study clinic in case of any disease or symptoms that arise between visits. AEs will be investigated at each follow-up visit. Each AE will be reported spontaneously or in response to general, nondirected discussion with the attending midwife/researcher or physician/researcher. All AEs, regardless of seriousness, severity, or presumed relationship to study therapy, will be recorded using medical terminology in the source document and on the AE page. Whenever possible, diagnoses will be given when signs and symptoms are due to a common aetiology. Investigators will record their opinion concerning the relationship of the AE to BCG vaccination on the AE page. AE reporting

When the investigator, or trained physician, becomes aware that a serious AE (SAE) has occurred, the appropriate reporting form will be completed, and a copy emailed to the local Institutional Review Board.

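### Because visits are fixed to age while BCG is given at birth or week 14, scheduled checks for BCG reactions are denser after early vaccination, so transient reactions could look rarer with delay at equal true risk

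*Protocol article*

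**What the plan says.** The section on follow-up and subject retention sets clinic visits "scheduled on day 7 and at weeks 2, 6, 10, 14, 15, 26, 28, 48 and 52 after birth". The list is the same for both arms. Data on three named BCG reactions (local abscess, suppurative lymphadenitis, disseminated infection) are collected at each of these visits, and the section on AE monitoring confirms that "AEs will be investigated at each follow-up visit". The section on intervention and co-interventions places vaccination within 24 hours of birth in one arm and at 14 weeks of age in the other.

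Among the secondary outcome measures, adverse events are counted through 52 weeks of life, so the window is tied to age. BCG scar, in the same list, is tied to time since vaccination (12 weeks after it). The secondary analysis describes safety by type, frequency and severity and names no starting point for the window.

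Between visits, mothers have a study phone and a notebook, illness is asked about by recall since the previous visit, and "The mothers will be invited and encouraged to consult the study clinic in case of any disease or symptoms that arise between visits". The plan of analysis includes data from unscheduled visits.

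**The concern.** The reactions of interest follow vaccination, but the visits follow age. How often anyone looks for a reaction at a given time after BCG therefore depends on the arm. Restarting the clock at vaccination in the analysis aligns the time axis but cannot recover checks that were never made, so an analysis plan alone cannot fully repair this.

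The safety of early versus late BCG is one of the stated purposes of the trial, adverse events are a listed secondary outcome, severe BCG disease in the early arm is a named ethical concern, and the data monitoring committee is to carry out an interim safety analysis. If reactions are looked for more often after early BCG, part of any excess in the birth arm could be due to detection. A reaction in the delayed arm could also go without a scheduled check for up to 11 weeks.

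**Working it through.** **Inputs.** Visit ages in weeks, from the follow-up section (day 7 taken as week 1): 1, 2, 6, 10, 14, 15, 26, 28, 48, 52. Age at BCG, from the intervention section: 0 or 14 weeks.

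**Formula.** Weeks since BCG = visit age − age at BCG.

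- Birth arm: 1, 2, 6, 10, 14, 15, 26, 28, 48, 52.
- Delayed arm: 15 − 14 = 1; 26 − 14 = 12; 28 − 14 = 14; 48 − 14 = 34; 52 − 14 = 38.

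**Scheduled checks within equal time since BCG**

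| Window after BCG | Birth arm | Delayed arm |
|---|---|---|
| 10 weeks | 4 (1, 2, 6, 10) | 1 (1) |
| 13 weeks | 4 (1, 2, 6, 10) | 2 (1, 12) |
| 14 weeks | 5 (adds 14) | 3 (adds 14) |
| 38 weeks | 8 (adds 15, 26, 28) | 5 (adds 34, 38) |

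The longest gap in the first 12 weeks is 6 − 2 = 10 − 6 = 4 weeks in the birth arm and 12 − 1 = 11 weeks in the delayed arm. The only times since BCG at which both arms are checked are weeks 1 and 14.

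**Length of observation after BCG** under the age-based window: 52 − 0 = 52 weeks against 52 − 14 = 38 weeks.

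**Direction and sensitivity (assumptions, not an estimate).** The protocol gives neither onset nor duration of reactions, nor the completeness of reporting between visits. Suppose the true risk is equal, onset is uniform over weeks 0 to 12 after BCG, checks through week 14 count, and a reaction is seen at a visit only if it is present that day. For a reaction lasting 4 weeks:

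- Birth arm: every onset from 0 to 12 meets a visit, 12/12.
- Delayed arm: onsets in weeks 0–1 and 8–12 meet a visit, 5/12.
- Ratio delayed/birth: 5/12 = 0.42.

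If a fraction r of the reactions missed at visits is captured in other ways, each proportion p becomes p + (1 − p)r.

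| Duration | r = 0 | r = 0.5 | r = 0.8 | r = 1 |
|---|---|---|---|---|
| 2 weeks | 0.50 | 0.83 | 0.94 | 1.00 |
| 4 weeks | 0.42 | 0.71 | 0.88 | 1.00 |
| 6 weeks | 0.58 | 0.79 | 0.92 | 1.00 |
| 8 weeks | 0.75 | 0.88 | 0.95 | 1.00 |
| 12 weeks | 1.00 | 1.00 | 1.00 | 1.00 |

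With a strict 12-week cut-off and r = 0 the direction can reverse: for reactions lasting 10 weeks the ratio is (11/12)/(10/12) = 1.1, and for 12 weeks it is (12/12)/(10/12) = 1.2.

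**The case against.** A reader might infer that reactions would appear several times rarer with delayed BCG. That needs detection by examination at scheduled visits only, and the protocol describes more: a phone, a notebook, recall since the last visit, encouragement to attend for any symptom, and analysis of unscheduled visits. The table above shows how quickly the ratio moves towards 1 as such capture improves. This objection stands against any stated size and against certainty about the direction. It does not remove the imbalance. Caregiver teaching is about signs of severe illness, the notebook's front-page reminder concerns contact with a clinic, physician or hospital, and recall has to span 11 weeks in one arm where it spans at most 4 in the other.

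A reader might also infer that the AE monitoring section contradicts itself, since it states "Potential AEs will be carefully monitored throughout the trial with specific questionnaires" and then "Each AE will be reported spontaneously or in response to general, nondirected discussion". The document does not support this. The AE definition gives the three BCG events as the potential AEs, and the follow-up section collects them by name at each visit. Read together, these passages mean directed questions for the BCG events and open questioning for AEs in general; the second sentence is loosely drafted.

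Further points are fair. Each arm does have a check at 1 and at 14 weeks after BCG, and the delayed arm also has checks at 34 and 38 weeks. Figures 2 and 3, cited for the schedule, could not be seen. The scar outcome at 12 weeks after vaccination has no matching birth-arm visit in the text, so the listed visits may not be complete. An age-based calendar is also what keeps the severe-illness comparison symmetric. None of these places a check in the delayed arm's 11-week gap, but the figures should be looked at before acting.

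**Conclusion.** The point holds in a limited form. The visit arithmetic is exact: 4 scheduled checks against 2 in the first 13 weeks after BCG, a longest gap of 4 against 11 weeks, and 52 against 38 weeks of observation after BCG. As written, the plan could make reactions that resolve within the gap look rarer with delayed BCG at equal true risk. Reactions that last until week 12 after BCG would still be seen.

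The size of the bias cannot be found from the protocol. It ranges from none, if reporting between visits is complete, to substantial for short-lived reactions, if reporting is poor. The conclusion assumes that the figures add no visits between 15 and 26 weeks of age. It concerns a secondary safety outcome; the primary comparison of severe illness in the first 14 weeks uses the same calendar by age in both arms and is not affected.

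**What to change.** 1. **Analysis.** Compare BCG reactions by time since vaccination over a window of equal length in both arms; 38 weeks is the longest the schedule allows. As the main or a sensitivity comparison, restrict to the checks both arms share, 1 and 14 weeks after BCG. Count there only reactions present at the check, because at week 14 the preceding visit was 4 weeks earlier in the birth arm (week 10) and 2 weeks earlier in the delayed arm (week 12). State in the report that ascertainment between the shared checks is unequal. This costs nothing in data collection, but the restricted comparison leaves out reactions that came and went between the two checks.

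2. **Data collection.** Add a brief scripted phone check for the three BCG reactions at about 16, 20 and 24 weeks of age, made by existing staff on the phones already issued and using the same questions as at clinic visits. In the delayed arm these fall 2, 6 and 10 weeks after BCG, matching the birth arm's visits and cutting the longest gap to 4 weeks. Making the calls in both arms keeps contact by age the same for the other outcomes.

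The cost is modest staff time, up to 3 × 2,200 = 6,600 short calls. The trial has been recruiting since July 2016, so the change comes part-way through, and infants followed before and after it will differ in ascertainment; the date should be recorded. Calls rest on the mother's report and the birth arm's visits on clinic attendance, so they narrow the gap without fully closing it.
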